### 2.6. Intervention

#### 2.6.1. Experimental Group

Participants will receive Tele-SSE intervention protocol, three times a week, for nine months. At the beginning of the intervention, an instructor will explain the training guidelines. All sessions will be followed by videoconference through the digital whiteboard placed in every early childhood education classroom. The SSE will be performed on a fine carpet of 200 × 80 cm, divided into 40 squares of 20 × 20 cm, adapted to participants’ morphological characteristics (i.e., squares size will be reduced). Participants will execute the SSE exercises divided in two tapestries simultaneously. The SSE includes a total of 200 different movement patterns which are classified, according to their difficulty, into three general levels: beginner, intermediate and advanced [39]. The beginner level has two sublevels, while the intermediate and advanced levels have 3 sublevels. The proposed intervention will include a progression along the first six levels until the advanced level 1. The greater levels will be combined with other patterns that include colors or flexible surfaces that make the task even more difficult and encourage cooperative work among participants. Likewise, participants will start with simple two-step movement patterns and, step by step, they will perform more complex patterns that will require a greater number of steps per sequence, multidirectional movements and even the performance of other motor skills, such as jumping with feet together, jumping on one leg, etc. Participants should not step on the dividing lines of the squares. Table 1 shows the progression of Tele-SSE training.

Table 2 displays the typical structure that will be followed for Tele-SSE sessions in the experimental group. During the sessions, an avatar will be assigned to each participant, aiming them to register and follow-up their progression, which could encourage the adherence to practice and motivation of participants. Prior to starting every session, the instructor will contact participants by videoconference and will explain to them the session, showing the patterns that are going to be carried out. The first activity, after the relevant general and specific warm-up, will consist of remembering the patterns learnt in previous session. Then, participants will proceed to learn and execute the patterns selected for that day, the number of which will fluctuate between three and five patterns depending on their difficulty. Once the patterns have been performed, children will go on to a cool-down, consisting of stretching and a short relaxation that will help them to return their bodies to their initial state, and move to the next class in a relaxed state. At the end of every session, participants will be asked for their opinion about the patterns they have learned during the session, as well as about the effort they felt after the session using the EPInfant scale [40]. Participants will rate the intensity of the work performed (from 0 to 10) during the cool-down and final reflections, considering the stress and fatigue they have felt during the execution of the session [41,42]. Finally, they will be reminded to go to the bathroom to wash themselves and drink water.

#### 2.6.2. Control Group

Participants will continue with their usual school routines and usual classes, carrying out the scheduled activities (handicrafts, cards, free play, etc.) and will only participate in assessments. Thus, they will not take part in Tele-SSE intervention.

### 2.7. Measures and Procedures

Several measures will be taken to assess the utility and effectiveness of Tele-SSE cognitive and motor program (Table 3).

All measures will be taken using valid and reliable instruments. However, before every assessment session, participants will complete a warm-up where tests procedure will be explained, including a specific familiarization trial before they are carried out. Intersession test reliability will be checked by repeating the tests two weeks after with some of the sample participants. The motor competence evaluation will be carried out applying the PREFIT battery [36], while the assessment of cognitive abilities will be performed using The National Institutes of Health (NIH) Toolbox Early Childhood Cognition Battery (CFB) [43]. The NIH—Early Childhood CFB is part of the NIH Toolbox [44], a comprehensive set of neurobehavioral measurements that quickly assess cognitive, emotional, sensory, and motor functions.

Before starting tests, a warm-up of 3 to 5 min will be carried out, including games consisting of running, jumping and joint mobility exercises. To increase participants’ imagination, motivation, and adherence to the tests, the PREFIT battery uses two fantasy stories that relate the battery tests to play and fun.

On the one hand, the PREFIT battery is the result of a systematic review based on scientific evidence that collects different tests to assess physical fitness in preschoolers. This battery is an efficient tool in terms of time and materials needed and easily applicable to several children at the same time [36]. It includes the following measures: Body mass index (BMI). This parameter is calculated as the quotient of participant’s bodyweight (in kilograms) divided by their height (in meters) squared. It will be measured in kg·m^−2^. Bodyweight and height will be measured using a digital scale with measuring rod. Children will be barefoot, standing upright and fully erect, to step onto the centre of the scales distributing their weight between both feet. In addition, they should look straight ahead, place both arms alongside the body and without making any movement to assess their height. Two measurements will be taken, both for bodyweight and height, considering the average of them for analysis.Waist circumference. This will be assessed using a non-elastic measuring tape. Children should wear light clothing and stand with their abdomen relaxed and arms crossed over their chest. From this position, the evaluator will encircle the participant’s waist with the tape measure at the level of the navel and parallel to the floor. The participant will then lower his/her arms to a relaxed and abducted position. The measurement will be carried out twice and the average of the two measurements taken for analysis.Handgrip strength. This test will be carried out with an analogue dynamometer with an adjustable grip. The children will stand with their elbow extended and without touching their body with the dynamometer, they will slowly and continuously squeeze for at least 2 s, alternatively with both hands. Two attempts will be made with the optimal grip setting and with a short rest between the two attempts. The best attempt from each hand will be taken for analysis. The result of this test will be recorded in kg.Lower limb strength. The standing long jump test with feet together will be used. The child will stand behind the jump line on a nonslip surface, with feet shoulder-width apart, flex the knees with arms in front of the body and parallel to the ground, swing arms, push off with force and jump as far as possible. After landing, the subject will remain in a stable position for the attempt to be considered valid. Two attempts will be made and the best of the two will be selected for further analysis. The result of this test will be recorded in cm.Speed-agility test. The 4 × 10 m test will be performed on a nonslip surface. For the execution of this test, two parallel lines will be drawn on the ground, 10 m apart from each other and with an evaluator on each line. On the signal of the evaluator, the child will run as fast as possible to the other line, high-five evaluator 2 and return to the initial line to high-five evaluator 1. Then, without stopping, he/she will repeat the same action until completing a total of 4 runs of 10 m each. The time taken by the child to complete the test is measured. The result is recorded in seconds.Balance. This will be assessed using the one-leg balance test. Participants will stand still on the ground with one leg flexed. Two attempts will be made with each leg, selecting the best time to hold that position with each leg. Result will be recorded in seconds.Cardiorespiratory fitness. The 20-m shuttle run test will be conducted. Children will run between two lines separated by 20 m. Speed will be controlled using an audio signal previously established. The test starts at 8.5 km/h, and the speed will increase by 0.5 km/h every minute. Participants will start at the first audio signal or beep. The test is finished when the participant stops due to fatigue or fails to reach the end line concurrent with the audio signal or beep on two consecutive occasions. The last half stage completed will be considered for analysis.

On the other hand, The NIH—Early Childhood CFB measures cognitive aspects from 3–6 years and includes tests for processes such as executive functions and attention, episodic memory, and language. It is an easy-to-use (through an iPad) and widely applicable test for different populations that includes [43,45,46]:Executive function and attention. The two tests within the battery will be performed: the flanker inhibitory control and attention test, a measure of inhibitory control in the context of selective visual attention, and the dimensional change card sort, related to the cognitive flexibility and attention. In the first one, children must focus on a stimulus while inhibiting attention to the flanking ones (fish flanked by two fish on each side). In the second one, two target pictures are presented which vary in two dimensions (shape and colour). Children must sort them as indicated by an audio-recorded cue word. These two tests can be applied to children between 3 and 7 years.Episodic memory. This will be assessed with the picture sequence memory test, with different versions for 3–4 and 5–6 years. In any case, children must reproduce previously-shown object sequences.Language. This will use the picture vocabulary test, which covers from 3 years and above. The children must select the picture that most closely matches the meaning of an audio-recorded word.

### 2.8. Statistics

Statistical procedures and analysis will be conducted using the Statistical Package for Social Sciences (SPSS, Version 25, IBM SPSS, Armonk, NY, USA) software. Personal data will be kept anonymous.

Kolmogorov−Smirnov and Levene’s test will be used to check the normality and homogeneity of data, respectively. Descriptive data will be expressed as mean and standard deviation (parametric variables) or median and interquartile range (nonparametric variables). Then, independent sample T-test (parametric variables) or Mann−Whitney U-test (nonparametric variables) would be performed to determine whether experimental and control groups are comparable at baseline in terms of participant characteristics. Likewise, to detect whether the cognitive and motor intervention consisting of a one-course (9 months) Tele-SSE program has a statistically significant effect on the motor and cognitive skills of preschoolers, an ANCOVA will be conducted using baseline of the main variable as covariate. Alpha level will be set at *p* ≤ 0.05. The magnitude of differences will be evaluated by Cohen’s d effect size. The effect size thresholds will be interpreted as follows: <0.2, small; 0.2 to <0.8, moderate; ≥0.8, large [47].

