## Abstract

Early childhood education aims to achieve the motor, cognitive, emotional, and social development of preschoolers by providing them with a variety of learning opportunities. The square-stepping exercise (SSE) is a balance and lower limb strength training programme used to prevent falls and stimulate cognitive function in older adults. This project aims to propose an SSE tele-exercise (Tele-SSE) protocol to evaluate its effects on the motor and cognitive development of children aged between 3 and 6 years. A randomized controlled trial with experimental (Tele-SSE) and control (general education) groups will be carried out. The application of Tele-SSE will be performed for 9 months (three times per week) and one additional follow-up after the intervention at the beginning of the next academic year. One-hundred and two preschoolers will be recruited and randomly distributed into the two groups: experimental (*n* = 51) and control (*n* = 51). Although the main outcome will be balance due to the nature of the SSE, outcomes will include physical and motor (body mass index, waist circumference, handgrip and lower-limb strength, speed-agility, and cardiorespiratory fitness) and cognitive (executive functions and attention, episodic memory, and language assessment, using the Fitness Assessment in the Preschool Battery (PREFIT) and The National Institutes of Health Toolbox—Early Childhood Cognition Battery. This project aims to improve cognitive and motor skills in preschoolers aged between 3 and 6 years old, based on a 9-month Tele-SSE intervention. If this intervention proves to be effective, it could be implemented in those centres, entities and associations specializing in early childhood education.

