### 2.3. Sample Size

Sample size computations were calculated based on normative values from the Fitness Assessment in the Preschool Battery (PREFIT) for children aged three years old (most heterogeneous population into the selected age range), specifically data from the one-leg balance test [36], because it will be the primary outcome in this study. Thus, accepting a 0.05 alpha risk and a 0.2 beta risk in a bilateral contrast and assuming a common standard deviation of 5.025 and a correlation coefficient of 0.7 between baseline and final measurement [37]; a total of 102 participants (51 subjects in the experimental group and 51 in the control group) are required to detect a difference equal to or greater than 2.43 units. A loss-to-follow-up rate of 20% has been considered.

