## Figures and Tables

**Table 1 ijerph-18-08649-t001:** Progression of Tele-SSE intervention proposal.

Month	Frequency (Days a Week)	Session Duration (min)	Steps per Sequence (Number)	Difficulty (Level)	Additional Difficulty Variables
1	3	60	2	Beginner 1	
2	3	60	4	Beginner 1 and 2	
3	3	60	4	Beginner 2	
4	3	60	6	Intermediate 1	
5	3	60	6	Intermediate 2	
6	3	60	6	Intermediate 3	
7	3	60	8	Intermediate 3	Colors
8	3	60	8	Advanced 1	Colors
9	3	60	8	Advanced 1	Flexible surface

**Table 2 ijerph-18-08649-t002:** Typical structure of Tele-SSE session.

Typical SSE Session Way
**Warm-up** (10 min)
General
Joint mobility
Stretching
Specific
Cognitive play
Motion game
**Main Part** (40 min)
Review of the patterns learnt in the previous session
Learning and implementation of SSE pattern 1
Learning and implementation of SSE pattern 2
Learning and implementation of SSE pattern 3
Learning and implementation of SSE pattern 4
**Cool-down** (10 min)
Stretching
Relaxation
Final thought
Personal hygiene

**Table 3 ijerph-18-08649-t003:** Assessments schedule for both experimental and control group.

Assessment	Baseline	Month 3	Month 6	Month 9	Beginning of Next Course
BMI	x	x	x	x	x
Waist circumference	x	x	x	x	x
Handgrip strength	x	x	x	x	x
Lower limb strength	x	x	x	x	x
Speed-agility	x	x	x	x	x
Balance	x	x	x	x	x
Cardiorespiratory fitness	x	x	x	x	x
Executive function and attention	x	x	x	x	x
Episodic memory	x	x	x	x	x
Language	x	x	x	x	x

BMI, body mass index; x, measure to be taken on that period of time.

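### Section 2.5 keeps only children assessed at every visit and Section 2.8 states one baseline-adjusted ANCOVA, so a five-visit schedule discards partial data and leaves next-course retention without a stated contrast

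*Protocol article*

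**What the plan says.** - **Schedule.** Table 3 ("Assessments schedule for both experimental and control group") marks all ten assessments at baseline, months 3, 6 and 9, and the start of the next course. The Abstract presents the last visit as a design feature: "one additional follow-up after the intervention at the beginning of the next academic year".
- **Efficacy analysis.** Section 2.8 gives one between-group test of the nine-month programme: "an ANCOVA will be conducted using baseline of the main variable as covariate". It contains no visit term and no comparison tied to follow-up, and it does not name the visit that supplies the outcome.
- **Analysis set.** Section 2.5, under the eligibility criteria, admits to the analysis only children with every assessment: baseline, the quarterly interim visits, final and follow-up. Children in the experimental arm must also have attended at least 80% of classes. The control arm has no matching condition.
- **Expected loss.** Section 2.3 says: "A loss-to-follow-up rate of 20% has been considered".

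**The concern.** Read together, Sections 2.5 and 2.8 make poor use of the schedule. A child with baseline, month-3, month-6 and month-9 scores leaves the primary analysis for missing the visit in the next school year. A child with months 3 and 6 but no month 9 is also lost, and would still be lost to a month-9 ANCOVA if Section 2.5 were relaxed.

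Three things are at stake:
- precision, because observed scores are thrown away;
- bias, if the children who leave differ in ways their earlier scores would show, or if the one-sided attendance rule selects the better children in one arm;
- the follow-up question: the next-course visit can remove children from the analysis, yet no stated contrast reports what happened there.

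**Working it through.** **Inputs from Section 2.3.** Two-sided alpha 0.05 and power 0.80 ("accepting a 0.05 alpha risk and a 0.2 beta risk in a bilateral contrast"); SD 5.025 ("assuming a common standard deviation of 5.025"); r = 0.7 ("a correlation coefficient of 0.7 between baseline and final measurement"); difference 2.43 ("are required to detect a difference equal to or greater than 2.43 units"); 51 per arm; 20% loss.

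**1. The plan's own figure.** The SD of change is 5.025 × √(2 × (1 − 0.7)) = 3.892. Then n = 2 × (3.892 × (1.960 + 0.842) / 2.43)² = 40.28 per arm, and 40.28 / 0.8 = 50.35, rounded up to 51. The stated 102 reproduces.

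**2. Power of the stated ANCOVA.** The residual SD is 5.025 × √(1 − 0.49) = 3.589. This needs 35 evaluable children per arm, or 44 after 20% loss. After 20% loss about 41 of 51 remain: SE = 3.589 × √(2/41) = 0.793 and power = Φ(2.43/0.793 − 1.96) = 86.6%.

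**3. Change the model, keep Section 2.5.** Every analysed child has all visits, so the month-9 contrast is the same in both models: 41 per arm, SE 0.793, power 86.6%. No child is recovered.

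**4. Amend Section 2.5 and use a mixed model, with random loss.** Suppose 10 children per arm leave after month 6. Let R² be the share of month-9 variance, given baseline, that months 3 and 6 explain. The effective number per arm is 1 / [(1 − R²)/41 + R²/51]. The interim correlations are not in the document, so two structures are assumed:

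| Assumed structure | R² | Effective n per arm | Variance ratio | SE | Power |
|---|---|---|---|---|---|
| 0.7 between all visits | 0.24 | 43.0 | 41/43.0 = 0.95 | 0.774 | 88.1% |
| Decaying to 0.7 over nine months | 0.585 | 46.3 | 41/46.3 = 0.89 | 0.746 | 90.3% |

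Simulation agrees: a variance ratio of 0.95 for the first structure and 0.87 to 0.89 for the second. If the losses fall evenly before month 3, after month 3 and after month 6, the effective numbers drop to 42.2 and 43.6 and power to 87.5% and 88.6%. The variance saving is then only about 3% (41/42.2 = 0.97) to 6% (41/43.6 = 0.94).

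**5. Cost of the all-visits rule itself.** If the 10 children per arm miss only the next-course visit, a plain month-9 ANCOVA without the rule uses all 51: SE 0.711, power 92.8% against 86.6%. As an illustration of how the rule accumulates, an assumed independent 5% missing at each of four post-baseline visits leaves 0.95⁴ = 81.5% complete; 10% leaves 0.90⁴ = 65.6%.

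**6. Loss related to earlier scores (illustration only).** Assume that Tele-SSE children with low month-6 scores leave more often (log-odds −0.3 per second, about 22% to 23% missing). In simulation, ANCOVA on children with a month-9 score averaged 2.70 to 2.97 against a true 2.43, an overstatement of 0.27 to 0.54 s. Type I error was about 6% to 10%. The likelihood estimate that uses months 3 and 6 stayed at about 2.43, with type I error near 5%.

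**The case against.** The strongest reply is that baseline-adjusted ANCOVA is a sound primary analysis, that it exceeds the planned 80% power on the plan's own inputs, and that an article may leave the handling of interim visits and missing data to a fuller document. Much of this stands. ANCOVA is not wrong, the trial is not underpowered because of it, and the precision gain is small.

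A reader might infer that the ANCOVA is what loses the children. The documents do not support that: Section 2.5 removes them before any model is fitted, and step 3 shows that a new model alone changes nothing at month 9. A reader might also take a month-9 test as stated. Section 2.8 names no visit; month 9 is inferred from the programme's length and from the baseline-to-final correlation in Section 2.3. Nor is it right that follow-up plays no part, since attending it is a condition of being analysed.

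The bias figures in step 6 come from one chosen mechanism in which leaving depends on an observed score, so the mixed model is unbiased by construction. Other mechanisms need not favour it. The one-sided selection that the document does state is the 80% attendance rule, and no choice of model repairs that.

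The reply does not reach Section 2.5. The restriction to complete attenders is a stated rule, not a detail left open, and it conflicts with collecting repeated scores while allowing for 20% loss.

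**Conclusion.** The point holds for Sections 2.5 and 2.8 taken together. As written, a child missing any one visit is excluded although other scores exist, the experimental arm carries an extra attendance filter, and retention at the next-course visit has no stated contrast.

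The size is modest under random loss: about 5% to 13% lower variance when losses come after month 6, less when they come earlier, and about 1 to 4 power points over the roughly 85% to 87% that ANCOVA already gives. These figures rest on assumed interim correlations and apply only if Section 2.5 is amended. Removing bias from loss related to earlier observed scores is a real advantage, but its amount cannot be read from the documents. This is a worthwhile, cheap improvement and not a fatal flaw.

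**What to change.** Amend both sections together.

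- **Section 2.5.** Remove the all-assessments and 80%-attendance conditions from the primary analysis. Analyse all randomised children with at least one post-baseline score, in the arm to which they were randomised. If wanted, keep the two conditions as a per-protocol sensitivity analysis.
- **Section 2.8.** Use one linear mixed model for repeated measures per outcome, with arm, visit, arm × visit, baseline and baseline × visit, an unstructured covariance and a named simpler fallback. State the month-9 arm contrast as primary and the next-course arm contrast as the secondary estimate of retention. Months 3 and 6 inform the model and need no separate tests.

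The cost is protocol or SAP wording and a few lines of syntax in the stated software, with no extra children or visits. The downsides are reliance on missing-at-random given the observed scores, and possible convergence trouble with about 100 children, which the fallback covers.

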## 3. Discussion

The implementation of SSE interventions has been shown to be effective in the older-adult population [28,29,30], as well as in specific populations, such as those with type 2 diabetes mellitus [33], multiple sclerosis [32], Parkinson’s disease [48] or fibromyalgia [39], among others. Thus, we hypothesise that a 9-month intervention based on Tele-SSE will improve motor and cognitive skills in preschoolers. More specifically, Tele-SSE will enhance static balance, physical fitness, body composition, strength, speed-agility, executive function and attention, processing speed, episodic and working memory and language use of preschool children.

This pedagogical proposal will be carried out telematically for several reasons. In addition to questions of motivation and adherence of the participants, as we are living in a pandemic context, as a tool to maintain security in the educational community: it would help to keep the bubble groups intact, and it would be a tool that could help to reduce the contact of teachers who attend several schools and must change location throughout their day, among others. In addition, the implementation of this pedagogical proposal through new technologies allows it to be implemented at any time during the school day and in different places at the same time, as it could be developed synchronously or asynchronously in different preschooler education classrooms in different public schools. Furthermore, its potential applicability to other populations is noteworthy due to its high adherence and viability as a consequence of its originality and its relatively low cost [31].

Regarding early years children, their holistic development is one of the main objectives to be achieved in any educational action or stage [1] and the necessary means and opportunities should be provided to stimulate all their developmental areas: motor, cognitive, emotional and social. To achieve this objective, educational psychomotor intervention should be a powerful tool to contribute to motor, cognitive, social, emotional, and academic skill development [5,9].

This protocol proposes the implementation of a Tele-SEE intervention using digital whiteboards, available in early years educational settings. It is an exergaming modality with great potential for stimulating children’s development, focusing on the motor and cognitive areas. Moreover, Tele-SEE has great potential due to its ease of implementation, the possibility of being used in groups and its wide possibilities of adaptation according to the children’s characteristics.

Therefore, the pedagogical proposal of an educational psychomotor intervention proposed through Tele-SSE would be pioneering, measuring the effectiveness of this type of intervention as a tool for improving motor development, especially balance, and cognitive development in preschoolers between 3 and 6 years. 

